## Abstract

**Background:**

Depression is a leading cause of disability in adolescents, however few receive evidence-based treatment. Despite having the potential to overcome barriers to treatment uptake and adherence, there are very few CBT-based smartphone apps for adolescents. To address this gap, we developed ClearlyMe®, a self-guided CBT smartphone app for adolescent depression and anxiety. ClearlyMe® consists of 37 brief lessons containing core CBT elements, accessed either individually or as part of a ‘collection’. Here, we describe the protocol for a randomised controlled trial aiming to evaluate the effect of ClearlyMe® on depressive symptoms and secondary outcomes, including engagement, anxiety and wellbeing, when delivered with and without guided support compared to an attention matched control.

**Methods:**

We aim to recruit 489 adolescents aged 12-17 years with mild to moderately-severe depressive symptoms. Participants will be screened for inclusion, complete the baseline assessment and are then randomly allocated to receive ClearlyMe® (self-directed use), ClearlyMe® with guided SMS support (guided use) or digital psychoeducation (attention-matched control). Depressive symptoms and secondary outcomes will be assessed at 6-weeks (primary endpoint) and 4-months post-baseline (secondary endpoint). Engagement, conceptualised as uptake, adherence and completion, will also be assessed 6-weeks post-baseline. Mixed-effects linear modelling will be used to conduct intention-to-treat analyses to determine whether reductions in depressive symptoms and secondary outcomes are greater for conditions receiving ClearlyMe® relative to control at 6-weeks and 4-months post-baseline and greater for intervention adherers relative to non-adherers. To minimise risk, participants will be encouraged to use the Get Help section of the app and can also opt to receive a call from the team clinical psychologist at baseline, and at the 6-week and 4-month post-baseline assessments when reporting suicidal ideation.

**Discussion:**

This is the first clinical trial examining a CBT smartphone app specifically designed for adolescent depression. It will provide empirical evidence on the effects of ClearlyMe® on depressive symptoms when used with and without guided support.

**Trial registration:**

Australian New Zealand Clinical Trials Registry (ACTRN12622000131752).

**Universal trial number:**

U1111-1271-8519.

## Background

Depression is a leading cause of disability in adolescents and can compromise social functioning, academic performance and emotional development [1, 2]. As up to 25% of adolescents worldwide, at any given time, experience elevated symptoms of depression [3], timely access to effective interventions is critical to prevent chronic, lifelong illness [4]. Cognitive behavioural therapy (CBT) is a structured, skills-based psychotherapy typically delivered by a trained clinician over several sessions [5, 6]. It is the gold-standard psychological treatment for depression [7–10] and is recommended as a first-line treatment in children and adolescents aged 5-18 years [11]. However, many adolescents do not seek professional help due to a range of barriers [12–15]. Among those who do seek treatment, many do not receive CBT [16, 17]. As a result, treatment outcomes for depressed adolescents remain poor. The limited access and uptake of CBT is a major barrier that needs to be rectified.

Digital CBT interventions have been developed to overcome clinician shortages and other barries impeding access to treatment. These interventions been shown to be effective for lowering symptoms of depression and anxiety symptoms among adolescents [18–20]. Several recent meta-analyses examining the effectiveness of computerised, web-based, and smartphone app-CBT interventions in adolescents have shown there are small to medium effects in favour of digital interventions over no-intervention controls (e.g., wait list controls) in reducing depressive symptoms at post-treatment, however, these interventions did not appear to provide superior effects to therapeutically active comparators (e.g., group or individual CBT) [18–21]. Individuals’ engagement with digital interventions is also suboptimal, with low levels of program completion compromising users’ exposure to critical elements of treatment, such as cognitive restructuring [20, 22]. For example, reported completion rates in trials of digital CBT average 57%, with a range of 0 to 100%, demonstrating substantial variability between interventions [18]. If improved engagement and completion of digital CBT interventions increases exposure and development of critical CBT skills, as demonstrated in in-person CBT [23, 24], it may increase the benefits of digital delivery, however this requires empirical validation.

Low engagement with digital CBT among adolescents does not appear to be due to their unwillingness to use digital technologies to address mental health concerns. Uptake of commercially developed mental health smartphone apps is substantial, with millions of downloads and thousands of active monthly users [25]. Despite widespread uptake, many commercially developed apps lack both proof of effectiveness and critical CBT elements [26]. Among evaluated mental health smartphone apps, two recent reviews collectively identified only three smartphone apps for adolescents that contained elements of CBT, with none specifically targeting adolescent depression [27, 28]. Young people have reported that many of the existing computerised CBT interventions are less visually appealing than commercially developed apps, with unrefined usability and content that is not aligned with their needs [20]. This may explain why comparisons of studies show smartphone mental health apps outperform computerised and web-based interventions in terms of engagement, with an average retention rate of 80% [28] compared to 57% [18], although there is substantial variability in completion rates between apps. Given high rates of ownership and uninhibited access to internet and multimedia functionality, smartphones offer a promising means of delivering CBT that is yet to be adequately exploited.

While engagement with existing evidence-based digital mental health interventions is poor, human support (also referred to as guidance) has been associated with increased adherence to digital mental health interventions [29] and improved outcomes [18, 20, 21], however also see [19, 30]. Human support can take various forms. It may be provided by therapists or non-therapists either in-person, via telephone, chat sessions or email [18, 21]. Support may consist of encouragement to use the intervention, motivational interviewing, feedback on activity completion or therapeutic support to implement strategies [18, 21]. There is some evidence to suggest young people prefer text-based support over telephone calls [31, 32]. However, the positive impact of this specific form of support on outcomes, adolescent engagement in digital CBT, or its effect on factors associated with increased likelihood of using a mental health app, such as perceived need for help, and beliefs about app effectiveness and usability [33], is unclear [19, 32, 34]. Specifically, little is understood about the superiority of smartphone CBT with text-based guided support in terms of benefit or in promoting engagement and adherence relative to unsupported use [35]. Developing this understanding through robust research may inform how digital CBT could be offered to adolescents to optimise engagement [27, 28].

To overcome the gaps in current treatment availability, the Black Dog Institute developed ClearlyMe® - a free, self-directed CBT smartphone app that provides therapeutic content and symptom management strategies for mild to moderately severe symptoms of depression and anxiety in adolescents. Adolescents helped develop the app through extensive co-design, described in detail in Li et al. [36]. The app contains 37 brief (up to 10 minutes in duration), non-sequential ‘lessons’ consisting of psychoeducation, cognitive restructuring (thought challenging and behavioural experiments), emotion awareness and acceptance, activity scheduling, behavioural activation, goal setting, problem solving, exposure, relaxation, mindfulness, and values identification. The lessons encourage participants to practise the psychological skills between periods of app use and return to the app to reflect or complete further content as needed. Users are encouraged to complete the lessons via nine curated ‘collections’, which are a structured program of lessons grouped together to target a specific set of symptoms. Each collection varies in length, taking approximately 20 minutes to complete. Users can also complete the individual lessons from a ‘show all’ list whereby they self-select lessons considered to be relevant to their individual needs. In this list, lessons are categorised into three groups depending on their target: ‘emotions’, ‘thoughts’, ‘behaviours’. The app also includes a MoodCheck (i.e., rating mood on a scale from awful to great to track changes in mood over time), MindHacks (i.e., quick strategies that help in the moment), and Stories (i.e., short videos of young peoples’ experience managing mental health symptoms and positive help-seeking experience) to provide users with additional pathways to access therapeutic content. For these features, specific lessons are recommended after the feature is accessed. ClearlyMe® also includes in-app reminders, ‘saving’ and ‘favourite’ functions to support users to return to the app to reengage in content. The app also includes a ‘Get Help’ section that contains information of when and where to access additional mental health support services. ClearlyMe® is the first self-guided smartphone app providing a comprehensive CBT intervention developed specifically for adolescent depression. A rigorous clinical treatment trial among adolescents with mild to moderately-severe depressive symptoms is now needed to determine whether ClearlyMe® is effective for improving depressive symptoms and for engaging young people in depression treatment delivered via their smartphone.

### Trial objectives

This protocol is reported following SPIRIT guidelines to facilitate the reporting of the trial results using CONSORT guidelines [37]. It describes the methodology for the MobiliseMe study. The primary aim of the MobiliseMe study is to evaluate the effectiveness of the ClearlyMe® app for reducing depressive symptoms in adolescents. Using a three-arm parallel-group randomised controlled trial (RCT), the MobiliseMe study will compare self-directed use of the ClearlyMe® app with guided use alongside an attention-matched control condition to determine the effectiveness of the app for improving self-reported depressive symptoms in adolescents with mild to moderately-severe depressive symptoms after 6-weeks of use (primary endpoint) and at 4-month follow-up (secondary endpoint). This study will also evaluate the secondary impacts of the ClearlyMe® app on anxiety symptoms, psychological distress, emotional wellbeing, quality of life, rumination, emotion regulation and CBT skill acquisition. Participants’ engagement with the ClearlyMe® app (i.e., app uptake, treatment adherence and completions) and its influence on outcomes will also be explored. Creating and reporting multiple measures of engagement facilitates an understanding of the multiple ways participants may engage with the intervention, allows comparison between interventions and follows recent recommendations [38].

### Hypotheses

The primary hypothesis is that relative to the attention control condition, participants who receive the ClearlyMe® app (self-directed or guided) will have greater reductions in self-reported depressive symptoms between baseline and 6-weeks post-baseline (primary endpoint), as well as baseline and 4-month follow-up (secondary endpoint). A secondary hypothesis is that relative to the control condition, participants who receive the ClearlyMe® app (self-directed or guided) will report greater improvements in anxiety symptoms, psychological distress, emotional wellbeing, quality of life, rumination, emotion regulation and CBT skill acquisition between baseline and 6-weeks post-baseline, as well as baseline and 4-month follow-up. It is hypothesised that participants who receive guided support to use ClearlyMe® will report significantly higher levels of engagement than those who do not, however, no hypotheses have been made regarding the effect of guided support on outcomes given mixed findings in the literature e.g. [19, 21, 30, 35]. Exploratory analyses will examine whether the intervention was more effective for certain subgroups of the sample (e.g., based on age, symptom severity at baseline, greater perceived need for care, and higher openness to digital mental health) and whether the effects of the intervention were driven by other variables, such as rumination, emotion regulation, CBT skill acquisition, digital therapeutic alliance, and measures of app engagement.

## Methods/design

### Trial design

This superiority trial will utilise a three-arm, parallel group randomised controlled trial design with an equal allocation ratio. Outcome measures will be assessed at baseline, post-intervention (primary endpoint, measured at 6-weeks post-baseline) and follow-up (secondary endpoint, measured at 4-months post-baseline). A 4-month follow-up was selected to ensure participants in the control condition were provided with the intervention after a reasonable duration and to reduce participant attrition. The University of New South Wales is the sponsor of this clinical trial and ethics approval was given by the University of New South Wales Human Research Ethics Committee (HC#210889). This trial was registered with the Australian New Zealand Clinical Trials Registry on the 27th of January 2022 (ACTRN12622000131752) and has been allocated the Universal Trial Number U1111-1271-8519.

### Setting

This trial will be conducted entirely online, using the bespoke Black Dog Institute Research Engine, purpose built from which to conduct research trials. Data will be collected from individuals residing in Australia.

### Participants

Eligible adolescents are those aged 12 to 17 years old; located in Australia; who own or have access to a smartphone; have access to the Internet, an active email address and mobile phone number; comfortable with reading English at Grade 7-8 level; and who can obtain their parent or guardian’s consent. Eligible adolescents must also report mild to moderately-severe depressive symptoms as determined by a total score ranging between 5 and 19 on the Patient Health Questionnaire for Adolescents (PHQ-A) at screening. Ineligible adolescents are those who are currently receiving or about to start psychological treatment from a mental health professional for symptoms of depression or anxiety; are currently taking or about to start a course of prescribed medication for symptoms of depression or anxiety; report severe suicidal ideation as determined by a score of ≥2 on item 9 of the PHQ-A; respond ‘yes’ to items asking whether within the past month they have had serious thoughts or intentions about ending their life, or have made an attempt to end their life; nil or severe depressive symptoms as determined by a total score of ≤4 or ≥ 20 on the PHQ-A; or fail to satisfy any of the inclusion criteria at screening. Uptake of other depression interventions during the trial is permitted and will be assessed at primary and secondary endpoints.

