### Randomisation and blinding

Randomisation will be carried out according to the International Council for Harmonisation guidelines [91]. Randomisation to one of the three trial arms will be conducted immediately after completion of the baseline assessment using a computerised randomisation procedure within the Black Dog Institute Research Engine. A stratified randomisation approach with a block size of 6 (1:1 ratio) will be used to ensure balance across the conditions in terms of age (12 to 14 years vs. 15 to 17 years), and symptom severity (mild [as determined by a total score of 9 or less on the PHQ-A] vs moderate to moderately-severe [as determined by a total score of 10 or more on the PHQ-A]). Allocation will be fully automatic, with no input from the research team. Participants will not be directly informed of their condition allocation; however, they may be able to deduce this based on differences in the study activities. For the primary outcomes analyses, the statistician will be blinded to participants’ allocations. The statistician will be unblinded when examining intervention completion rates due to differences in the total number of modules/lessons across each condition as well as when conducting exploratory moderator analyses. Key members of the research team not involved in data analysis, including research assistants providing guided support, will be unblinded to participants’ allocation as they will require access to the Black Dog Institute Research Engine to contact participants if they experience adverse events and to provide support to participants allocated to the guided use condition.

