
### Monitoring

The current trial will utilise a Trial Management Group to supervise the overall conduct and safety of the trial in accordance with the National Health and Medical Research Council (NHMRC) guidelines on Data Safety Monitoring [92]. Details about this group are published on the Australian New Zealand Clinical Trials Registry (see here). As this trial includes symptomatic adolescents, each study assessment will include a list of mental health services and support resources suitable for adolescents. Participants who report an Adverse Event (AE), which includes severe suicide ideation (indicated by a score of ≥2 on item-9 of the PHQ-A) reported at baseline or the primary or secondary end-points and severe depressive symptoms (indicated by a total score ≥ 20 on the PHQ-9-A) reported at the secondary endpoint, will be offered a follow-up call from a Clinical Psychologist who will conduct a risk assessment over the phone. If at risk, the participant will be advised to contact an appropriate service. Parents will be contacted if the risk of harm is deemed imminent or the participant requests it. All adverse events and serious adverse events will be formally recorded and reported to the Trial Management Group in a monthly report and to the University of New South Wales Human Research Ethics Committee by the Clinical Trial Manager. No interim analyses on primary or secondary outcomes are planned, unless it is warranted by safety reports or upon the request of the Trial Management Group. The Trial Management Group may recommend pausing or terminating the trial if they have concerns for participant safety, based on (but not limited to) a higher than anticipated rate of one or more of the primary endpoints. At any time, the University of New South Wales can audit trial conduct and this process will be independent from the investigators and the sponsor.

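### A PHQ-A item 9 score of 2 or more at baseline is defined as an adverse event, although baseline comes before allocation and before any intervention

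*Protocol article*

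**What the plan says.** Under Participants, adolescents are ineligible if they "report severe suicidal ideation as determined by a score of ≥2 on item 9 of the PHQ-A". The section Procedure and participant timeline has eligibility determined by an online screener. Registration follows, then parental consent (up to 1 week), then the baseline assessment (up to 7 further days).

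Under Randomisation and blinding, "Randomisation to one of the three trial arms will be conducted immediately after completion of the baseline assessment", and "Allocation will be fully automatic, with no input from the research team".

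Under Monitoring, adverse events include "severe suicide ideation (indicated by a score of ≥2 on item-9 of the PHQ-A) reported at baseline" or at either follow-up. Participants with such an event "will be offered a follow-up call from a Clinical Psychologist who will conduct a risk assessment over the phone". Those found to be at risk are advised to contact a service, and parents are contacted if harm is judged imminent or the participant asks for it. On reporting, "All adverse events and serious adverse events will be formally recorded and reported to the Trial Management Group in a monthly report"; the ethics committee is informed too. On consequences, "The Trial Management Group may recommend pausing or terminating the trial if they have concerns for participant safety".

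**The concern.** An adverse-event count tells an oversight group what has happened to participants since they were exposed to the trial's interventions. A score given before allocation cannot carry that information for any of the three arms. Under the definition as written, such scores belong to the same class as item 9 scores at 6 weeks and 4 months, and they go to the group that can recommend a pause. Read literally, the trial's adverse-event total would include events that measure who was recruited rather than what the interventions did.

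There is a related question about entry. The score that excludes an adolescent at screening is expected to occur at baseline as well, and the article does not say what it then means for entry.

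**Working it through.** The article states no figure to reproduce. The check is a comparison of sections, with a little arithmetic.

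**1. Order of events** (Procedure and participant timeline; Randomisation and blinding). Screener, registration, parental consent, baseline, automatic randomisation, intervention, 6-week assessment, 4-month assessment.

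**2. Time points in the adverse-event definition** (Monitoring). Item 9 ≥2 counts at baseline, 6 weeks and 4 months. Against the order in step 1, the first falls before allocation and the other two after it. The item 9 adverse-event count is therefore

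total = baseline + 6 weeks + 4 months,

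and no intervention can have contributed to the first term.

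**3. Possible size of the baseline term.** The article gives no baseline item 9 rate, so the rate p is an assumption. With N = 489 (Sample size), expected baseline events = 489 × p:

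| Assumed p | 489 × p | About |
|---|---|---|
| 1% | 4.9 | 5 |
| 2% | 9.8 | 10 |
| 5% | 24.5 | 24 |

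**4. Can item 9 change between screening and baseline?** The two windows allow 7 + 7 = 14 days from registration, and screening comes earlier still. The PHQ-A covers the previous 14 days (Outcomes, Depressive symptoms). The share of the baseline recall period that the screener also covered is max(0, 14 − gap)/14:

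- gap 1 day: 13/14 = 93%
- gap 7 days: 7/14 = 50%
- gap 14 days: 0/14 = 0%

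The windows are upper limits and the usual gap is unknown. A new score of 2 or more at baseline is therefore possible, and Monitoring expects it.

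**5. What stopping these adolescents would cost.** To randomise 489, 489/(1 − p) must complete baseline. Each adolescent stopped loses two scheduled risk checks (6 weeks and 4 months). Allowing for the 20% attrition in Sample size at each follow-up (the article states it only to the primary endpoint; using it at 4 months is an assumption), the checks lost are 2 × 0.8 = 1.6 per adolescent stopped.

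| Assumed p | Baseline completers needed | Stopped | Checks lost (×2) | With 20% attrition (×1.6) |
|---|---|---|---|---|
| 1% | 493.9 | 4.9 | 9.9 | 7.9 |
| 2% | 499.0 | 10.0 | 20.0 | 16.0 |
| 5% | 514.7 | 25.7 | 51.5 | 41.2 |

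**The case against.** **On the adverse-event definition.** The label sets off the clinical response and the formal record, and recording an event does not claim that an intervention caused it. Each score belongs to a named assessment, so baseline events can be separated. The layout of the monthly report is not given, and table layout is commonly left to a fuller document. Most of this stands: a reader might infer that baseline and later events are pooled into one total, and the article does not say so. What remains is the definition itself, which the article does state. It puts a score that precedes every intervention in the class of events reported to the oversight group.

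**On entry to the trial.** A reader might infer that the trial lets in adolescents whom its own safety rule excludes, and that a stop before allocation is needed. The documents do not support that reading, for four reasons.

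- No sentence says outright that these adolescents are randomised. Allocation without team input does not rule out an automated rule; an automated stop would itself need no team input.
- The case is foreseen and answered with an offered call, a risk assessment, service advice and conditional parental contact. Unblinded staff have system access so that they can "contact participants if they experience adverse events", whatever the arm. The Recruitment section adds crisis information at the end of the baseline survey.
- By baseline the team holds contact details and parental consent, which it lacks at screening. Different handling at the two points is coherent.
- The article identifies no hazard from being allocated to the app, the app with SMS support, or the flyers. A stop would take away two later risk checks per adolescent.

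It is fair to say in return that the call is optional (Abstract, Methods) and that no rule for this case is stated. That supports asking the sponsor for a statement of intent, and no more.

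**Conclusion.** The point holds for the adverse-event definition. Followed as written, Monitoring counts item 9 scores recorded before any intervention as adverse events and sends them to the group that may recommend a pause. This is a fault of classification. Its size is unknown: the figures of about 5, 10 or 24 events rest entirely on assumed rates of 1%, 2% and 5%. Nothing in the article shows that baseline events would be pooled with later ones or would lead to a pause.

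The entry question is a matter for clarification. Whether to stop adolescents who score 2 or more at baseline is a design choice with costs on both sides.

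Allocation follows baseline and is automatic in all arms, so neither matter implies a difference in protection between arms or a bias in the primary analysis.

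**What to change.** **Required.** Amend Monitoring so that item 9 ≥2 at baseline is recorded as a pre-randomisation finding. Keep every part of the present response: the offered call, the risk assessment, the service advice and the parental-contact rule. Continue to report these findings to the Trial Management Group and the ethics committee, but tabulate them separately from post-allocation adverse events in the monthly report and in the final safety table. Cases already recorded can be reclassified by the assessment at which the score was given. The cost is one extra row, with no new data and no change in care.

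**For clarification.** State in one sentence whether an adolescent who scores 2 or more on item 9 at baseline is meant to be randomised. If the sponsor chooses to stop them, the Research Engine could apply the rule before allocation, as it already withdraws participants for missing consent or a late baseline. That choice would forgo the risk checks shown in the working. Because the first participant was enrolled on 12 May 2022, it would also leave the trial with two entry rules. The date of the change would then need reporting, and those already randomised would stay in the intention-to-treat set.
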